### Objective and research questions

The Victoria intervention is a novel intervention. Although the intervention is thoughtfully designed and piloted, due to its novelty it is important to study the implementation process and its context. Therefore, we will perform both a trial and a process evaluation to study the effectiveness and feasibility of this intervention. In addition, it is not only important to examine whether the intervention is effective as a whole, it is also relevant to further examine which clients will or will not benefit from the intervention [36].

The aim of this initial trial on the Victoria intervention is to gain insight into the implementation process and effectiveness of the Victoria intervention, on both the team level and the client level, in reducing victimization, including other adversities, and increasing societal participation. The primary research questions are:To what extent is the Victoria intervention implemented as intended and how is this new intervention perceived by the MHP?Does applying the Victoria intervention lead to increased societal participation and decreased victimization compared to care as usual (CAU) for clients of outpatient teams with SMI?

Secondary research questions are:Is the Victoria intervention an effective intervention for clients with SMI with regard to acknowledgement of adversities, quality of life, psychosocial functioning, and self-efficacy, compared to CAU?Is the Victoria intervention an effective intervention compared to CAU, with regard to awareness and acknowledgement of victimization by MHPs, and their insight in societal participation of the client?

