To achieve this, a multi-method design will be used. First, qualitative interviews will be carried out with several professionals and clients. MHPs of the outpatient teams are purposefully selected, including the trainers of the intervention and management staff from the two involved sites. Twenty clients participating in the RCT will be selected and asked for consent. These interviews will take place from a year after the training for the RCT. A topic list will be used to steer the interview. The interviews with the professionals will focus on understanding perceptions regarding the relevance of: the intervention, the training and the supervision meetings, the implementation as a whole, and the feasibility of using the intervention in real life. The clients will be asked if they noticed obvious differences in the conversations with their case managers with regard to adversities in the social context, and how they perceive these differences. Data will be audio recorded, transcribed verbatim, and coded using the ATLAS software program. Second, the supervision sessions will be recorded and analyzed to examine whether professionals implemented the Victoria intervention as intended, and to get a better picture of their experiences with and perceptions of the intervention. Third, during the supervision sessions, the professionals will be asked to fill out a checklist to inquire their knowledge about the steps of the intervention. This is done to measure fidelity of the intervention. Fourth, in the RCT questionnaires for the intervention teams, questions are added about the extent to which the professional has executed the intervention in real practice, and on the insight the professional has in potential adversities that act as a barrier for clients’ participation. Both the checklist and the questionnaire are analyzed using SPSS (version 22).

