#### Measures

Table 1 provides an overview of the measurement instruments used. These instruments were chosen according to their comparability in national and international mental health research, and their psychometric characteristics. Duration and sensitivity to measure change were also taken into consideration. The first author as well as trained interviewers will carry out the interviews, which will take place on a location preferred by the client, at home or at team location. The interviewers were trained by explaining the topic list and using role-play, in order minimize bias due to inter-reviewer differences. Moreover, the first one or two interviews will be performed in dyads, with the researcher. Data will be entered into a secured database by researchers or research assistants. Participants’ names will be changed into randomly assigned numbers of which only two of the authors have the key.

**Table 1 Tab1:** Overview of measurement instruments

Concept	Instrument	Level	T0	T1	T2^a^
Primary outcome measures					
Societal participation	Birchwood Social Functioning Scale (SFS)	Client	x	x	x
Criminal victimization	The Safety Monitor, section 4	Client	x	x	x
Discrimination and stigmatization	Discrimination and Stigma Scale (DISC-12)	Client	x	x	x
Perceived safety	The Safety Monitor, section 3	Client	x	x	x
Secondary outcome measures					
Acknowledgement of adversities	Structured questionnaire on feelings when discussing adversities	Client	x	x	x
Knowledge on rehabilitation and adversities	Structured questionnaire	MHP	x	x	x
Self-efficacy	Mental Health Confidence Scale (MHCS)	Client	x	x	x
Quality of Life	Manchester Short Assessment of Quality of Life (MANSA)	Client	x	x	x
General psycho-social functioning	The Health of the Nation Outcome Scales (HoNOS)	MHP	x	x	x
Additional and control measures					
Socio-demographic characteristics	Structured questionnaire	Client	x	x	x
Primary diagnosis	Structured questionnaire	MHP	x		
Number of years in MHC	Structured questionnaire	Client	x		
Social Support	Inventory of Social Reliance	Client	x	x	x
Neighborhood nuisance	The Safety Monitor, section 1 and 2	Client	x	x	x
Perpetration	The Safety Monitor, section 5	Client	x	x	x
FACT fidelity	CCAF scores	Team	x		x
Adherence to rehabilitation principles	Treatment plan (sample of 15% per team)	Client	x		x

^a^*T0* baseline, *T1* 9 months follow-up, *T2* 18 months follow-up

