#### Secondary outcome measures

The following secondary outcome measures will be used to gain more insight into the effects of the Victoria intervention.*Acknowledgement of adversities* related to societal participation is assessed through a self-report questionnaire developed for this study.*Knowledge on rehabilitation and adversities* will be measured through questions for MHP on the domains and phases of the BPR, and through questions on recent conversations about adversities. These questions are also developed for this study.*Self-efficacy* in mental health-related beliefs is measured through the Mental Health Confidence Scale (MHCS) [48], with a 6-point Likert scale, ranging from ‘totally no confidence’ to ‘full confidence’. Cronbach’s alpha for the total scale is 0.93 [49].To measure the *quality of life* the Manchester Short Assessment of Quality of Life (MANSA) is used [50, 51]. The MANSA has good internal consistency (α = 0.72) and is highly correlated (*r* = > 0.83 for each domain) with the Lancashire Quality of Life Profile (LQLP) [50]. The scale consists of 12 questions with a 7-point Likert scale ranging from ‘couldn’t be worse’ to couldn’t be better’ and 4 questions that are answered with yes/no.*General psycho-social functioning* is measured through the Health of the Nation Outcome Scale (HoNOS), a scale that is standard in MHC in the UK [52]. The MHP scores each item on a scale from 0 to 4. The intra class correlation coefficient is 0.92, Cronbach’s alpha is 0.78 and it correlates well with other scales [53]. Moreover, the HoNOS is sensitive to measure change in people with SMI.

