A final strength of the study is the multi-method approach. A process evaluation will be conducted to examine the implementation process of the intervention. Studies with a similar target population that examine complex interventions in a RCT often find no treatment effect, due to, for example, implementation or fidelity issues [62]. Within the design of an RCT, normally, there is little room for examining the implementation process, leading to a black box in explaining the results. Therefore, the UK Medical Research Council advises conducting a process evaluation, to understand context mechanisms and provide insights on implementation and fidelity [63]. For this reason, we do include a process evaluation and a longitudinal follow-up on effects, using a cluster RCT.

One of the main challenges in this study lies in the fact that the Victoria intervention is a complex intervention, encompassing characteristics of the local context, and the complexity of causal relations between intervention and outcomes [36]. MHPs in the participating teams sometimes work in multiple teams or, due to reorganization, they shift from one team to the other. This brings challenges in the implementation of the intervention. To address this, a strong collaboration is created between the two MHC institutions and the university in this project, with shared goals and input. Additionally, the process evaluation will be helpful in following the implementation process.

Another challenge of this study, and of most other studies among outpatients with SMI and follow-up measurements, is the dropout risk in the cluster RCT. In the sample size calculation, we take this into account by estimating a 15% loss to follow-up, and using effect sizes that may be considered conservative, compared to effect sizes found in other studies [64]. This leads to 347 required respondents at baseline measurement. Moreover, with the help of the MHPs, a contact plan, and by giving clients incentives for participating, we aim to prevent dropout as much as possible.

Finally, due to novelty of the Victoria intervention, there is no valid fidelity measure. Therefore, in this project a new fidelity checklist will be developed and used. To increase validity in measuring fidelity, we use triangulation by also including qualitative analyses of the recordings of the supervision meetings and questionnaires for both clients and MHP, as explained in the methods section.

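### Professionals' insight, one part of a secondary question posed against care as usual, has no described measure in control teams, and use of Victoria elements there is not measured directly

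*Protocol article*

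**What the plan says.** In the protocol article, the second secondary question under Objective and research questions is comparative. It asks whether Victoria is effective against care as usual "with regard to awareness and acknowledgement of victimization by MHPs, and their insight in societal participation of the client".

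The section Process evaluation lists four sources of data. The fourth is introduced as follows: "Fourth, in the RCT questionnaires for the intervention teams, questions are added". One set of these items asks how far Victoria was put to use. The other set, named in the same sentence, is "on the insight the professional has in potential adversities that act as a barrier for clients’ participation". Both sets of items are thus assigned to the intervention teams.

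Table 1 under Measures lists a secondary outcome called "Knowledge on rehabilitation and adversities", completed by professionals at T0, T1 and T2. Secondary outcome measures says that it "will be measured through questions for MHP on the domains and phases of the BPR" and also through questions on recent talks about adversities. No arm restriction is given. Statistical analyses applies to secondary outcomes the same between-condition procedure as to the main outcomes.

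Randomization and blinding stratifies team allocation by organization and promises to monitor staff changes and clients who switch teams, with correction in the analysis. The Discussion adds that "MHPs in the participating teams sometimes work in multiple teams" or move between them after reorganization.

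**The concern.** A question posed against care as usual needs the same measurement in both arms. Where insight is asked about only in teams that were trained, any change from baseline in those teams is uncontrolled: it cannot be separated from time trends, from the effect of being asked repeatedly, or from the BPR training and supervision that all teams received beforehand.

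The second issue is interpretation. The process evaluation exists to help understand the trial's effects. If the client outcomes show no difference, one explanation to examine is that some control clients were seen by professionals who already used parts of Victoria. The items that ask directly about carrying out the intervention are not planned for control teams.

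**Working it through.** No figure in the article bears on this point, so the check is a side-by-side reading.

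**Step 1. Split the secondary question and look for a measure of each part in both arms.**

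| Component | Measure described | Both arms? |
|---|---|---|
| Awareness of victimization | Professionals' questions on recent talks about adversities (Table 1; Secondary outcome measures) | Yes, no arm restriction |
| Acknowledgement of victimization | The same questions; also the client questionnaire on feelings when adversities are discussed | Yes, no arm restriction |
| Insight in the client's societal participation | No item under that name. The nearest are the insight items in Process evaluation | No, intervention teams only |

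**Step 2. Check whether another professional-level measure supplies insight.** The remaining half of the professionals' questionnaire tests knowledge of the domains and phases of the BPR. Care as usual says all teams get the same basic BPR training before randomization, so that sites are comparable in BPR knowledge and skills. That makes these items a weak test of what Victoria adds, although they could still diverge during follow-up. The HoNOS is completed by professionals, but it rates the client's functioning. Neither is described as a measure of insight.

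**Step 3. Compare the constructs.** The research question concerns insight in the client's participation; the process-evaluation items concern insight in adversities that block participation. If the latter are the intended measure, there are no control data. If they are not, no insight measure is described for either arm. The sections need reconciling in both cases.

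**Step 4. List what could reveal use of Victoria in control teams.**
- Monitoring of staff changes and client switching covers people who move.
- Professionals' answers on recent talks, and clients' answers on discussing adversities, could show a shift in control teams. They are indirect, because such talks can occur without Victoria.
- Items on execution of Victoria are direct, but are placed in the intervention teams' questionnaires.
- A professional who holds posts in two teams throughout has not changed post, so monitoring of changes does not clearly capture that person. Because allocation is stratified by organization, both arms can be expected within each organization, and such dual posts may span arms.

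**The case against.** The strongest reply has four parts.

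1. Asking only the implementing teams about implementation is ordinary practice in a process evaluation, and nothing says that the process-evaluation items are meant to answer the secondary question. This is fair for the execution items. It does not help the insight component, which is then left without any described measure.

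2. The BPR domains (housing, social contacts, education, work) are the same domains that the first Victoria step explores, so BPR questions might reflect insight in participation. That is possible, and it is why these items should be kept. But knowing the domains and phases of a method is not the same as insight into a particular client's participation.

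3. The professionals' questionnaire was developed for the study and its items are not shown; the full protocol may contain insight items for both arms. This stands as a limit on certainty. The point does not rest on silence alone, however, because the article states which teams receive the added items.

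4. Contamination is already addressed through monitoring and indirect items. This largely stands. A reader might infer that the whole question on professionals lacks a control comparison, or that contamination could not be seen at all. The documents support neither: the questions on recent talks carry no arm restriction and are compared between conditions, and staff and client moves are tracked.

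**Conclusion.** The point holds in limited form. As the article stands, the insight component of one secondary question has no described control comparison, while awareness and acknowledgement have one. Use of Victoria elements in control teams is measured only indirectly, with a gap for professionals who work in several teams at once.

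No primary outcome or analysis is affected. The size cannot be put as a number. The article gives neither the extent of shared staffing nor the number of teams per arm, so a calculation of how far contamination would dilute the effect would rest on assumed shares. It would also describe contamination itself, not the consequence of failing to measure it.

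The conclusion assumes that the article describes the professionals' questionnaire correctly and that its mention of the intervention teams is meant literally. If the full questionnaire already asks control professionals about insight, a sentence saying so would settle the first part.

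**What to change.** - In Process evaluation and Secondary outcome measures, place the insight items in the professionals' questionnaire of both conditions at T0, T1 and T2. State whether they concern insight in participation, in adversities that block it, or both, so that they match the research question.
- Name the insight items, together with the existing questions on recent talks, as the outcome for this secondary question. Report the BPR-knowledge items separately.
- Extend the monitoring in Randomization and blinding: for each participating client, record whether the case manager attended Victoria training or also works in an intervention team, and report this by arm.

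The cost is small: a few items in a questionnaire already listed for professionals at all three time points, and one staffing record per client. The form becomes slightly longer for control professionals, and the wording must be neutral so that it does not teach them the four steps. If T0 has already been collected without these items in control teams, that baseline cannot be recovered. Adding them at T1 and T2 would still give a between-arm comparison at follow-up, to be reported as lacking a control baseline.

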### Cluster RCT

#### Recruitment and consent

Clients eligible for participation receive a letter and brochure with information about the study, as approved by the ethical committee. In this letter, the themes of the study, questionnaire and time frame are explained. Clients are also informed that during the study they can withdraw at any time. After a two-week consideration period, the researchers will contact the client to ask if more information is needed and if they are willing to participate. If the client is willing to participate, a date, time, and place for the interview is scheduled. Clients will be asked to give their written informed consent before the start of the baseline interview. Participants will receive a compensation of 5, 10, and 15 euros for T0, T1, and T2 respectively.

Because randomization is performed at a team level and the Victoria intervention is considered a team approach, no separate informed consent is needed for the group randomization and consequently having the Victoria conversation. However, if the client wishes not to talk about societal participation and related adverse events, MHPs have to respect that.

#### Randomization and blinding

The participating teams will be randomly allocated to either the experimental or control condition by an independent senior researcher at Tilburg University, stratified by mental health organization. Cluster randomization was chosen as individual randomization would mean reassigning clients from their regular case managers and was therefore considered to be ethically undesirable. Moreover, cluster randomization reduces risks of contamination between the intervention and control group, as the intervention method is team based. We will monitor staff changes as well as clients switching teams to correct for in statistical analyses.

Due to the nature of the intervention, both the MHP and researchers cannot be unaware of the allocation to the conditions, but they are strongly advised not to disclose to the participating clients whether they receive care from an experimental or control team.

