#### Primary outcome measures cluster RCT

The first primary outcome measure is *social participation *measured with the Birchwood Social Functioning Scale (SFS) [44]. It measures social functioning on seven domains: social engagement/withdrawal, interpersonal behavior, pro-social activities, recreation, independence-competence, independence-performance, and employment/occupation. The SFS is a reliable, valid, sensitive to change, instrument with a high internal consistency (α = 0.80) [44].

The second primary outcome measure is victimization related to societal participation and includes the following:2.*Criminal victimization* will be measured with the Dutch version of the Safety Monitor, developed by the Dutch Ministry of Security and Justice [45], and strongly resembles the International Crime Victimization Survey [46]. It is a self-report questionnaire in which section 4 measures victimization on 15 crimes: burglary, theft from car, car theft, theft of other motorized vehicles, bicycle theft, (attempt to) robbery, theft (other than previously categorized), sexual intimidation or assault, threats (of violence), physical assault, vandalism, identity fraud, fraud with buying/selling items/services, hacking, cyber bullying. For each incident reported in the past 12 months, participants are asked to give more information about the incident.3.*Perceived safety* will also be measured with the Safety Monitor. The participant is asked whether they ever feel unsafe (yes/no) and how often (often/sometimes/rarely).4.*Discrimination and stigmatization* is assessed by the Discrimination and Stigmatization Scale (DISC-12) [47]. This scale consists of four subscales: unfair treatment, stopping self, overcoming stigma, positive treatment. The DISC-12 contains 32 items answered on a 4-point scale ranging from ‘no difference (0)’ to ‘a lot (3)’. A ‘not applicable’ answer is available when the participant was not involved in the described situation. Psychometric properties are considered good, Cronbach’s alpha is 0.78 and the inter-rater reliability ranges from 0.62 to 0.95.

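### Unblinded researchers help collect all four self-reported primary outcomes for a reason that fits only the trained professionals, so part of the interviewer-bias risk is avoidable

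*Protocol article*

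**What the plan says.** Under Randomization and blinding, the protocol article gives the nature of the intervention as the reason that "both the MHP and researchers cannot be unaware of the allocation to the conditions". The safeguard it adds concerns the clients: "they are strongly advised not to disclose to the participating clients whether they receive care from an experimental or control team".

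Under Measures, "The first author as well as trained interviewers will carry out the interviews". The client chooses whether to be seen at home or at the team's premises. Interviewers are trained with a topic list and role-play "in order minimize bias due to inter-reviewer differences", and the first one or two interviews are done jointly with the researcher. Table 1 lists all four primary outcomes at client level: social functioning (SFS), criminal victimization and perceived safety (Safety Monitor), and discrimination and stigma (DISC-12). Of the Safety Monitor the article says: "It is a self-report questionnaire in which section 4 measures victimization on 15 crimes".

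Under Process evaluation, "Twenty clients participating in the RCT will be selected and asked for consent". On timing, "These interviews will take place from a year after the training for the RCT". These clients are asked whether they noticed a change in how their case manager talks with them about adversities. Under Design, the last outcome interview (T2) is at 18 months.

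**The concern.** The reason offered and the conclusion drawn do not match. The intervention is a four-step conversation held by trained mental health professionals. They cannot be masked, and neither can a researcher who runs the training or the process evaluation. Someone who only reads out questionnaires and records answers has no such need to know the arm.

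The safeguard masks the client from the condition, not the assessor, and the interviewer training targets differences between interviewers, not differences that follow the arm. Some instruments leave room for discretion: each reported crime is followed by further questions on the incident, and the DISC-12 has a not-applicable option. If probing or recording differs by known arm, the difference goes straight into the treatment comparison, and neither the mixed model nor a larger sample removes it.

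The process interviews raise a second, smaller question. A client asked before T2 about changed conversations on adversities may infer the condition, or may answer the same topic differently at T2. That would work against the client masking the plan asks for.

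**Working it through.** **Who knows allocation, and who measures**

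| Role | Knows allocation? | Collects primary outcomes? |
|---|---|---|
| Mental health professionals | Yes, stated | No |
| Researchers, which presumably includes the first author | Yes, stated | Yes, the first author |
| Trained interviewers | Not stated | Yes |

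The second row is where the stated reason falls short. The third row is open.

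**Scale of the planned effect**

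Inputs from Sample size: r = 1, ρ = 0.20, v = 0.25, two-sided α = 0.05, power 0.80. σ is not given, so σ = 1 is assumed. The number of measurements T is not given either.

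N = (z₀.₉₇₅ + z₀.₈₀)² σ² (r + 1)[1 + (T − 1)ρ] / (v² r T)

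- T = 1: 251.2
- T = 2: 150.7, rounded up to 151, the plan's figure
- T = 3: 117.2

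So 151 per arm reproduces with T = 2 and σ = 1, and 0.25 can be read in SD units. It is stated for social functioning only.

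**Illustration of interviewer bias (assumed sizes)**

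The documents give no bias figure. Take an average shift b between arms when there is no true effect, and ignore clustering:

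SE = √[(2/151) × 1.2/2] = 0.0891 SD

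P(reject) = 1 − Φ(1.96 − b/SE) + Φ(−1.96 − b/SE)

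| b (SD) | b / 0.25 | Two-sided false-positive rate |
|---|---|---|
| 0 | 0% | 0.050 |
| 0.05 | 20% | 0.087 |
| 0.10 | 40% | 0.202 |

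Clustering by team would widen the SE and lower these rejection rates, but the estimate would be shifted by the same amount.

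**Process interviews**

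- The window opens 12 months after training and T2 is at 18 months. If training coincides with T0, the overlap is 18 − 12 = 6 months.
- The Discussion gives a 6-month inclusion period. If training follows its end (an assumption), the first recruits are 6 + 12 = 18 months past T0 when the window opens, so there is no overlap for them; the last recruits still have about 6 months.
- Share of the sample: 20/302 = 6.6% of all clients at T2, or at most 20/151 = 13.2% of one arm.
- If all 20 are in one arm and each shifts by an assumed 0.25 or 0.50 SD, the arm mean at T2 moves by 0.132 × 0.25 = 0.033 or 0.132 × 0.50 = 0.066 SD. In a T2-only comparison, with SE = √(2/151) = 0.115, the false-positive rate becomes 0.060 or 0.089.

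**The case against.** The strongest reply is that the article says less than the concern needs. A reader might infer that every interviewer is declared unblinded. The blinding statement names professionals and researchers; the Measures section uses trained interviewers as a separate term and is silent on what they know. How they are briefed may be set out in the full protocol. That stands, so the firm part of the point is confined to the first author and any other researcher who interviews.

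Masking would also leak. Interviews may take place at the team location, and clients who notice changed conversations can mention them, not least when answering the questionnaire on feelings when discussing adversities. This also stands, but it argues for partial masking with a recorded guess, not for none. Both arms receive the same basic rehabilitation training, so talk of rehabilitation alone does not identify the arm. Largely fixed-response instruments and joint first interviews limit discretion, without addressing knowledge of the arm.

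A reader might also infer that 20 intervention clients will be debriefed and unmasked before T2. The article sets only an earliest date. It gives neither the arm of these clients nor the lag from T0 to training, and the question can be put without naming a condition. All clients have also met the study themes in the information letter and the same instruments at T0 and T1, so the added priming may be slight.

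Finally, moving every interview away from researchers would mean roughly 151 × 2 arms × 2 visits = 604 interviews. The article does not give the number of interviewers, so the feasibility of a complete transfer is not shown.

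**Conclusion.** The concern holds in limited form. The stated reason does not explain why researchers who know allocation must take part in collecting the four self-reported primary outcomes, and the risk that follows is partly avoidable at low cost. The documents do not establish that all interviewers are unblinded, or that bias will occur.

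Its size cannot be derived from the documents. The 0.05 to 0.10 SD range is a chosen illustration, measured against an effect planned for one outcome; other primary outcomes include yes/no items to which that scale does not carry over. The direction is unknown, since more attention to adversities could raise or lower what is reported.

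The timing of the process interviews is the lesser part. An interview before T2 is permitted, not stated, and the 13% ceiling requires all 20 to be intervention clients seen before T2. It calls for a scheduling rule and does not by itself threaten the result.

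**What to change.** 1. Withhold team allocation from the trained interviewers already planned, and assign T1 and T2 interviews to them as far as existing capacity allows.
2. Where a researcher who knows allocation must interview, spread those interviews evenly over both arms and record the interviewer for every interview. This keeps interviewer and arm from being confounded and allows a sensitivity check; it does not remove bias within an unblinded interviewer.
3. Have interviewers record a guess of condition at T2.
4. Hold each client's process interview after that client's T2 interview.
5. State in the blinding section which roles know allocation and which do not.

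The cost is less freedom in scheduling and slightly longer recall in the process interviews. None of this changes the sample size. Dropping the 20 clients from the outcome analysis would be a poorer answer: with 131 and 151 clients, or 141 in each arm, power falls from 0.80 to about 0.77 under the plan's own inputs.
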